## Abstract

**Background::**

There is no sufficient evidence on the effectiveness of acupuncture for neuropathic pain. This protocol describes a study that aims to evaluate the effectiveness and safety of electroacupuncture combined with conventional medicine for patients with intractable neuropathic pain, when compared with conventional medicine alone.

**Methods/design::**

This study is a prospective, open-labeled, randomized, cross-over clinical trial. A total of 40 patients with neuropathic pain who had a numeric rating scale (NRS) score of over 4 despite receiving conventional treatment for more than 3 months will be enrolled. Participants will receive conventional treatment for neuropathic pain (treatment C) or treatment C combined with 12 additional sessions of electroacupuncture treatment (treatment A) for 6 weeks. Participants will be randomly assigned to 1 of the 2 sequence groups (AC and CA group) with a 1:1 allocation. The differences of responder in the composite efficacy outcomes, which consist of the NRS, Brief Pain Inventory-Short Form (BPI-SF) pain subscale, and global assessment at 6 weeks after randomization will be examined as the primary outcome. Secondary outcomes include differences in the NRS, the Short-Form McGill Pain Questionnaire, BPI-SF, Fatigue Severity Scale, Hospital Anxiety and Depression Scale, Medical Outcomes Study Sleep Scale, global assessment, EQ-5D, and incremental cost-effective ratio at 6 and 15 weeks after randomization. Adverse events, vital signs, and physical examinations will be recorded to evaluate safety.

**Discussion::**

The study protocol for this trial will provide up-to-date evidence on the effectiveness and safety of electroacupuncture for patients with intractable neuropathic pain. The results will be disseminated through a peer-reviewed journal and conference presentations.

**Trial registration::**

Clinical Research Information Service, ID: KCT0003615. Registered on March 12, 2019. https://cris.nih.go.kr/cris/search/search_result_st01_kren.jsp?seq=13410& ltype=&rtype=

## Introduction

1

Neuropathic pain develops after injury to the nervous system, and is often accompanied by maladaptive changes in the somatosensory nervous system.^[1]^ The symptoms of neuropathic pain are often abnormally exaggerated by painful stimuli, and can even be provoked by non-painful stimuli. This could easily progress to chronic and refractory pain, which presents a great challenge in terms of management. Conventional pharmacological treatments for neuropathic pain include antidepressants and antiepileptics;^[2]^ however, the number of patients who achieve satisfactory pain relief is low, and is only 10% to 25% more than patients receiving placebo.^[3]^ Moreover, high comorbidity rates accompanied by chronic neuropathic pain, such as insomnia, anxiety, or depression,^[4]^ further makes the treatment challenging, and patients seek alternative treatment strategies including acupuncture treatment.^[5]^

Some studies have proposed the mechanisms of acupuncture for pain reduction. The local analgesic effects of acupuncture are mediated by adenosine A1 receptors^[6]^ or inactivation of the myofascial trigger point.^[7]^ Acupuncture analgesia can also be induced segmentally by the gate-control theory of pain. Needling of some acupuncture points located at the extremities can generally reduce pain through descending inhibitory pain control by serotonin and noradrenaline.^[8,9]^ Recently, clinical evidence on acupuncture for chronic pain, which is similar to nociceptive pain, has been well-established through many systematic reviews^[10–12]^ and clinical guidelines.^[13,14]^ A meta-analysis assessing 20,827 individual patient data from 39 trials suggested that acupuncture is an effective treatment option for chronic pain, including nonspecific musculoskeletal pain, osteoarthritis, headache, or shoulder pain, and that its effects persist over time, with only a small decrease at 1 year.^[11]^ The guidelines published by the American College of Physicians recommend that acupuncture should initially be selected for patients with chronic low back pain.^[13]^ However, when focusing on neuropathic pain such as diabetic neuropathy, chemotherapy-induced peripheral neuropathy, postherpetic neuralgia, or failed back surgery syndrome, there is no sufficient evidence on the effectiveness of acupuncture.^[3]^

Our pilot study^[15]^ explored effectiveness of electroacupuncture (EA) for patients with moderate to severe neuropathic pain despite already receiving conventional oral medications, and assessed the feasibility of a large-scale trial. The results showed that EA significantly decreased the intensity of pain in neuropathic patients, especially burning sensations, electric shock-like pain, and mechanical hyperalgesia. Furthermore, the number of acupuncture sessions was a significant factor for favorable results of reducing pain intensity. Based on our previous trial, we designed a large-scale, prospective, open-labeled, randomized, cross-over clinical trial to evaluate the effectiveness and safety of 12 sessions of EA for the treatment of neuropathic pain.

## Methods and design

2

### Objective

2.1

The aim of this study is to determine the effectiveness and safety of EA treatment for neuropathic pain when added to conventional neuropathic pain pharmacotherapies compared with no EA treatment. The pain intensity, function, quality of life, global assessment, and adverse events will also be assessed.

### Design and setting

2.2

This study is a prospective, open-labeled, randomized, cross-over clinical trial conducted at Seoul National University Hospital (SNUH) Pain Center and Kyung Hee University Korean Medicine Hospital (KHUKMH) in South Korea.

#### Recruitment strategy

2.2.1

A total of 40 patients with chronic neuropathic pain who did not achieve satisfactory pain relief despite receiving conventional treatment for more than 3 months will be recruited in SNUH Pain Center. The expected recruitment period is from December 2019 to May 2021. Participants will be recruited through advertising on the bulletin boards of the hospital, internet homepages of the hospital, public institutions, and through the media.

#### Study plan

2.2.2

This study is a cross-over trial that aims to compare conventional medical treatment (treatment C) with conventional medical treatment and an add-on EA treatment (treatment A) for patients with intractable neuropathic pain. A cross-over design was planned in which participants will be randomly assigned to 2 groups (AC and CA groups) according to the 2 treatment sequences.

Screening will be conducted after receiving written informed consent from the participant at SNUH Pain Center (Visit 1). They will then be randomly assigned to 1 of the 2 sequence groups: the AC group and CA group (Visit 2). The first treatment period will be conducted for 6 weeks. In the case of “treatment A”, during the treatment period, a total of 12 EA sessions will be performed for 6 weeks at KHUKMH. After the first treatment period, evaluations will continue at SNUH Pain Center (Visit 3). After a washout period of 2 weeks, participants will undergo a pain evaluation period for 7 days (Visit 4). If the average numeric rating scale (NRS) pain score, which is self-recorded in a diary, is 4 points or more during this period, patients will proceed to the second treatment period. If it is less than 4 points, the same “treatment C” will be maintained. The second treatment period will also be conducted for 6 weeks, as in the first treatment period, followed by a final evaluation (Visit 5). Figure 1 shows the study procedure and details.^[16]^

**Figure 1 F1:**
[figure not shown]
Modified CONSORT flow diagram for crossover trials. Intervention A: add-on electroacupuncture treatment; Intervention C; conventional treatment; EA: electroacupuncture.

### Types of participants

2.3

#### Inclusion criteria

2.3.1

Participants who meet the following conditions will be included:

1.Patients aged 19 years and over at screening.2.Patients who have peripheral neuropathic pain and satisfy criteria A) and B), and have criterion C) or D) identified on examination, depending on the conditions.A)Have a confirmed medical history of diagnosis for neuropathic pain according to clinical findings.B)Symptoms, history, and physical examination of patients suggest peripheral neuropathic pain.C)Electromyography/nerve conduction study or evoked potential test suggest peripheral neuropathy.D)Ultrasonographic examination at screening reveals lesions that indicate peripheral entrapment syndrome or peripheral neuropathy.3.Have unsatisfactory pain relief despite appropriate conservative treatment for more than 3 months before screening.4.Have a score ≥13 on the Korean version of the PainDETECT Questionnaire (PD-Q) at screening.5.Have an average score ≥4 on the NRS measured by a pain diary during the 7-day screening period before randomization.6.No evidence of disease recurrence in cancer survivors.7.Patients who can voluntarily consent to the study, understand the process of the study, and adequately write a reportable questionnaire.

#### Exclusion criteria

2.3.2

Participants will be excluded if any of the following conditions are satisfied:

1.Have other severe pain not related to the target disease that could cause confusion during pain assessment at screening or randomization.2.Use prohibited concomitant therapies within 7 days prior to screening, or change to concomitant medications with restricted usage within 14 days prior to screening.3.Have a clinically significant unstable nervous system, ophthalmological disease, hepatobiliary disease, respiratory disease, blood disease, cardiovascular disease, or mental disease within 12 months before screening.4.Used EA treatment at the affected area within 1 month before screening.5.Are pregnant, breastfeeding, or expecting a pregnancy during the study period.6.Have implanted medical devices such as spinal cord stimulators, implantable drug delivery systems, pacemakers, automatic defibrillators, aneurysm clips, vena cava clips, and skull plates.7.Have brain damage, symptomatic brain metastases, or epilepsy.8.Have abnormal skin conditions that would prevent proper application of the EA treatment.9.Are participating in other interventional clinical trials within 30 days before screening or present.10.Have severe bleeding tendency: low doses of oral aspirin and a general dose of antiplatelet/anticoagulant medication generally do not limit study participation, but only when apparent risk is predicted by the investigators judgment.11.Use immunosuppressive drugs.

### Randomization and allocation concealment

2.4

The randomization table was generated using SAS Version 9.2 (SAS institute Inc., Cary, NC) to assign patients to the AC group or CA group in a 1:1 ratio by the block randomization method. After obtaining informed consent, participants who satisfy the inclusion/exclusion criteria will be allocated on a web-based basis according to this randomization table. A random allocation table will be created at the Medical Research Collaborating Center (MRCC) of SNUH, and will be operated through web random allocation. The outcome assessors, data managers, and statisticians will be blinded to the allocation.

### Intervention

2.5

The EA treatment was modified from our pilot study,^[15]^ which was developed through a consensus of acupuncture specialists based on western medical acupuncture techniques as well as traditional meridian theory. EA treatment will be performed by Korean medicine doctors who graduated after 6 years of Korean medical college education and have at least 8 years of clinical experience. A total of 12 acupuncture sessions for 6 weeks will be performed using 0.25 × 40 mm disposable sterile acupuncture needles (Dongbang Acupuncture Inc., Chungnam, South Korea), which will be retained for 15 minutes. Up to 20 acupuncture points will be chosen by the practitioner based on traditional Asian medicine and western medical perspectives^[8,17]^ for local, segmental, and general stimulation. Local stimulation is defined insertion of the needle at a classical acupuncture point, tender point, or trigger point near the painful area. Segmental stimulation is insertion of the needle around area innervated by the same meridian or spinal nerve as that of the painful region. If direct needling to the local and segmental points exacerbates the pain, perisegmental points that are close to the affected segment, such as those above and below the area, or those on the opposite side of the equivalent contralateral segment will be used. Distal points which are located in the extremities for general stimulation will be chosen to treat the comorbidities of chronic pain according to traditional theory, such as insomnia (PC6, HT7, BL62, or KI6), depression/anxiety (PC6, HT7, LI4, or SP6), or fatigue (ST36, SP6, LU8, or GB20).

Electrical stimulation will be delivered using an EA device (ES-160, Ito Co., Ltd. Tokyo, Japan) with 2 Hz (local points), 2 to 6 Hz (local points or distal points), 120 Hz (segmental points), or 2 to 120 Hz (distal points) (altering every 2 seconds, 0.5 to 10 mA) approximately 80% of the maximum intensity.

### Permitted and prohibited concomitant treatments

2.6

Existing oral and transdermal drugs (opioids, tramadol, non-steroidal anti-inflammatory drugs, steroid, muscle relaxants, topical capsaicin, neurotropin, prostaglandin, local anesthetics, vitamin B1 and B12, and nefopam) should be taken at the existing dose from screening to the end of the study. Depending on the pain intensity, additional prescription of oral acetaminophen is allowed as a rescue medicine for analgesic purposes. If acetaminophen is used, the participant should record the dose of acetaminophen and date in the patient diary. Anticonvulsants and antidepressants, which were being used to control symptoms of existing neuropathic pain, are also taken at the maintenance dose during the study period. Only when there are safety problems with the use of these drugs, dose reduction or discontinuation of these drugs will be permitted if necessary.

Subjects who received interventional therapies such as nerve block, iontophoresis, laser therapy, spinal cord irritation, and transcutaneous electrical nerve stimulation have a minimum washout period of 7 days prior to their first visit. These therapies are prohibited in the study period. Other forms of pain relief therapy for neuralgia such as psychotherapy and physiotherapy can be continued from 14 days prior to the first visit if the frequency of therapy does not change; however, these are not allowed to start during the study period.

### Outcomes

2.7

#### Primary outcome measurement

2.7.1

The proportion of participants who achieved improvement, as measured by the predefined composite efficacy outcome (CEO) [NRS decreased from baseline + pain interference scale (PIS) in the Brief Pain Inventory-Short Form (BPI-SF) decreased by more than 20% from baseline + “minimally improved”, “much improved”, or “very much improved” in patient global impression change (PGIC)] at 6 weeks after randomization, will be used as the primary outcome measurement.

#### Secondary outcome measurements

2.7.2

Secondary outcomes include the differences in NRS score, the short-form McGill Pain Questionnaire, the BPI-SF, the Fatigue Severity Scale, the Hospital Anxiety and Depression Scale, the Medical Outcomes Study Sleep Scale, PGIC, EQ-5D-3L, PD-Q, Patient Satisfaction Scale, and incremental cost-effective ratio at 6 and 15 weeks after randomization will be measured.

#### Safety outcome measurements

2.7.3

Safety will be examined on every visit by measuring vital signs, performing physical examinations, and recording adverse events (AEs). For vital signs, the degree of change after the treatment period compared to before the treatment period will be summarized as mean, standard deviation (SD), median, minimum, and maximum value. The results of the physical examination will be summarized by the frequency and ratio. AEs will be summarized by the number and ratio of patients who experience AEs and serious AEs. The human chorionic gonadotropin urine test will only be performed in fertile women at the first and fifth visits.

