### Adverse events

2.11

Participants will be asked to report any AEs including those induced by EA throughout the study period at each visit. The expected AEs related with EA treatment include treatment-related pain, bruising, bleeding, or infection at the local site, nausea, dizziness, or anxiety.^[8,19]^

If AEs occur during the clinical trial, researchers will investigate the severity of symptoms, relevance to the intervention, action related to the intervention, treatments for AEs, and the result and seriousness of AEs. In the event of serious complications, researchers will provide adequate treatment to patients and terminate the EA treatment early if the patients find it difficult to continue the study. After that, a report will be prepared and submitted to the institutional review board (IRB).

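### No pregnancy test is scheduled between screening and the final visit, so fertile women in the CA sequence start electroacupuncture about 10 weeks after their last test, against about 1 week in AC

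*Protocol article*

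**What the plan says.** Section 2.7.3 (Safety outcome measurements) fixes the testing schedule: "The human chorionic gonadotropin urine test will only be performed in fertile women at the first and fifth visits". Section 2.2.2 (Study plan) makes Visit 1 the screening visit, Visit 2 randomisation, Visit 3 the evaluation after period 1, Visit 4 the pain evaluation after washout, and Visit 5 the final evaluation.

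Pregnancy is an exclusion in section 2.3.2, which bars women who "Are pregnant, breastfeeding, or expecting a pregnancy during the study period". The only condition that section 2.2.2 gives for moving into period 2 is a mean diary NRS of at least 4; pregnancy is not mentioned there.

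Other safety monitoring takes place throughout. Section 2.7.3 has vital signs, physical examination and adverse events recorded at every visit, and section 2.11 adds: "Participants will be asked to report any AEs including those induced by EA throughout the study period at each visit".

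**The concern.** In a cross-over trial the experimental treatment starts at two different times, depending on sequence. A pregnancy test at screening and another at the end would suit a parallel trial in which everyone starts treatment soon after screening. Here that holds only for AC. In CA, EA begins after period 1, washout and the diary week, and no scheduled test falls in between.

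A pregnancy that began during those weeks and that the woman has not recognised would not be found by a scheduled test before her first EA session. The Visit 5 test could show afterwards that exposure had occurred but could not prevent it. Pain eligibility is re-checked at Visit 4, just before half of the participants are due to receive EA for the first time; the pregnancy criterion is not.

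What is at stake is participant safety as the protocol itself defines it through its exclusion. The statistical properties of the trial are not involved.

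**Working it through.** **Inputs**

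- Screening to randomisation: about 1 week, from the diary in section 2.3.1, "measured by a pain diary during the 7-day screening period before randomization".
- Period 1: 6 weeks (section 2.2.2).
- Washout 2 weeks, then a 7-day pain evaluation at Visit 4 (section 2.2.2).
- Period 2: 6 weeks, then Visit 5 (section 2.2.2).
- Tests at Visits 1 and 5 (section 2.7.3).
- 20 participants per sequence and 20% planned drop-out (section 2.8).

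**Reproducing the plan's own figure.** Counting from randomisation, Visit 5 falls at 6 + 2 + 1 + 6 = 15 weeks. This agrees with the last assessment time in section 2.7.2: "incremental cost-effective ratio at 6 and 15 weeks after randomization will be measured". If the diary week lay inside the washout, the total would be 6 + 2 + 6 = 14 weeks, which does not agree. The diary week therefore follows the washout.

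**Timetable, in weeks from randomisation**

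| Event | Week |
|---|---|
| Visit 1, hCG test | about -1 |
| Period 1 (EA in AC) | 0 to 6 |
| Washout | 6 to 8 |
| Diary week, Visit 4 | 8 to 9 |
| Period 2 (EA in CA) | 9 to 15 |
| Visit 5, hCG test | 15 |

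**Time from last scheduled test to EA** (week of EA minus week of test)

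| | First EA session | Last EA session |
|---|---|---|
| AC, as planned | 0 - (-1) = 1 week | 6 - (-1) = 7 weeks |
| CA, as planned | 9 - (-1) = 10 weeks | 15 - (-1) = 16 weeks |
| CA, with a test at Visit 4 | 0 to 1 week | 6 to 7 weeks |

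The last row is a range because section 2.2.2 does not say whether Visit 4 opens the diary week (week 8) or closes it (week 9). Even if the first test were done on the day of randomisation, the CA interval to first EA would be 9 - 0 = 9 weeks. A longer screening lengthens the AC and CA intervals equally, so the difference of 9 weeks remains. Both intervals assume that EA starts promptly when its period opens.

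**How many women, and how often.** The number of fertile women in CA is not given. The ceiling is 20, or 20 × 0.8 = 16 if the planned drop-out all happens before period 2; the true number is probably far lower. For scale only, assume 1 to 8 fertile women and a yearly conception risk of 1% to 10%. Expected conceptions in 10 weeks are women × (1 - (1 - yearly risk)^(10/52)):

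- low end: 1 × (1 - 0.99^(10/52)) = 0.002
- high end: 8 × (1 - 0.90^(10/52)) = 0.16

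**The case against.** The strongest reply is that nothing here contradicts itself. Section 2.3.2 lists entry criteria, the Visit 1 test checks pregnancy at entry, and no other entry criterion apart from the pain score is re-checked before period 2. This stands, and the point is accordingly a design choice that could be better, not a misstatement. The exclusion nevertheless extends to pregnancies expected at any time in the study period, so the protocol's own interest in pregnancy does not end at entry.

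Second, the protocol gives no reason for the exclusion and lists no pregnancy-specific harm among the expected EA adverse events in section 2.11. The reason might be the background drugs in section 2.6, which both sequences take throughout; the difference between AC and CA would then carry no special meaning. This also stands as a limit on how much weight the point can bear.

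Third, the figures of 0.002 to 0.16 overstate the relevant event. They count all conceptions, while the gap concerns unrecognised ones. Some pregnancies would be known and could surface at a visit. Women expecting a pregnancy are already excluded. CA participants with a diary NRS below 4 stay on conventional treatment and receive no EA, and some will have dropped out. This is right: the figures are an upper guide under assumed inputs. It makes the event rarer still, but an examination and adverse-event questions cannot reliably find an unrecognised pregnancy.

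Fourth, the article is condensed, and contraception rules, withdrawal on pregnancy or testing on clinical suspicion may be in the full protocol. The restrictive word in section 2.7.3 may also mean merely that no one but fertile women is tested. Granted; the point therefore concerns scheduled tests. On either reading the article names the visits at which the test is done, and Visit 4 is not one of them.

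**Conclusion.** The point holds. As scheduled, the last pregnancy test precedes the first EA session by about 1 week in AC and about 10 weeks (at least 9) in CA, and in CA the next test follows all 12 sessions. The intervals rest on the stated visit timetable, which reproduces the 15-week final visit, on a screening of about 7 days, and on EA starting promptly in its period.

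The practical size is small. Few women are likely to be affected, an unrecognised pregnancy in the interval is rare, and no specific harm is documented. Type I error, power, sample size and the primary analysis are not affected. Confidence is high for the intervals but does not extend to clinical importance, on which the documents give no evidence. This is a worthwhile, inexpensive safety improvement and not a major flaw; it should be made because it applies the protocol's own exclusion equally in both sequences.

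**What to change.** Amend section 2.7.3 so that the urine hCG test is done in fertile women at Visits 1, 4 and 5, at least for those in CA, and require the Visit 4 result to be known before the first EA session of period 2. If Visit 4 opens the diary week, the result is at most about a week old when EA starts, as in AC; if it closes the week, the test must simply be read before treatment begins.

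The cost is one extra urine test per fertile woman in CA: at most 20 tests, and 1 to 8 under the assumption used above. The visit already exists, already includes a safety examination, and the test is already used in the trial. The amendment is one line but would need to go to the review boards of both institutions named in section 2.12. The downside is that an occasional CA participant with a positive test would not start EA.
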